## Abstract

**Background:**

The role of antibiotics in surgical procedures where the risk of surgical site infection (SSI) is low remains uncertain. There is, to date, no evidence to justify the routine use of antibiotics in postoperative reduction mammaplasty. The aim of this study is to evaluate the effect of postoperative antibiotic treatment on the occurrence of SSI after breast reduction surgery.

**Methods:**

This is a double-blind randomized clinical trial with 124 breast hypertrophy patients allocated to two treatment groups: antibiotic (*n* = 62) and placebo (*n* = 62). All patients will undergo reduction mammoplasty, performed by the same surgical team. The surgeons will raise the nipple-areola complex by the superomedial pedicle technique. The patients will receive antibiotics intravenously during anesthetic induction and every 6 hours thereafter during their 24-hour hospital stay. During discharge from the hospital, each patient will receive a numbered package containing either cephalexin or placebo capsules and will be directed to take one capsule every 6 hours for 7 days. Neither the surgery team nor the patients will know the contents of the capsules. Patients will be monitored for the occurrence of SSI once weekly during the first 30 days following hospital discharge by a single surgeon who is blinded to their treatment group. SSI will be evaluated based on the definition adopted by the Centers for Disease Control and Prevention.

**Discussion:**

Due to the variety of risk factors for SSI and limited case studies, conclusions regarding the effect of antibiotics on the occurrence of SSIs following reduction mammaplasty are potentially biased. In recent studies, perioperative antibiotic prophylaxis was effective in preventing infection and is therefore recommended in clinical practice. However, antibiotic use in the postoperative period still remains controversial.

**Trial registration:**

Clinicaltrials.gov Identifier: NCT02569866. Registered on 4 October 2015.

## Background

Surgical site infections (SSIs) are defined as wound infections that occur after invasive procedures and remain among the most common infections, accounting for 14–16% of all nosocomial infections in hospitalized patients. In recent years, greater attention has been paid to the study, prevention and control of SSIs by surgeons, health care professionals, and patients [1–4].

In a literature review of potential factors affecting the occurrence of SSIs, Junker et al. noted that the timing of antibiotic administration and the occurrence of surgical glove perforation significantly influence the occurrence of SSIs. Other factors, such as patient anemia, blood transfusion during surgery, and surgeon experience were not significant [3].

In many surgical procedures where the SSI risk is low, the role of antibiotics remains uncertain. Despite the lack of evidence of efficacy from randomized controlled trials, its use in plastic surgery is widespread in order to offer patients greater presumed safety standards, because even minor infections are able to interfere with the healing process and therefore the aesthetic result [4–11].

The prophylactic use of antibiotics was first studied by Krizek et al., in 1975. These authors evaluated the prescribing habits of surgeons over 10 years and demonstrated an increased use of prophylaxis during this period [3, 5, 12–15]. In a recent review article, Sajid et al. concluded that prophylactic antibiotic therapy reduces the risk of SSI after breast surgery and the risk of adverse reactions to this therapy was not significant [16].

SSIs related to breast surgeries occur at rates ranging from 0.8 to 36%, which is the highest among clean surgeries as a whole (rate lower than 5%). This variation can be attributed to the type of breast surgery performed, patient comorbidities, duration of postoperative follow-up, intraoperative complications and the availability of institutional information [17–19]. Nevertheless, there is, to date, no evidence to justify the routine use of antibiotics in the postoperative of reduction mammaplasty, and there is no consensus regarding its prescription, even among surgeons of the same department [14, 20–22].

The Centers for Disease Control and Prevention (CDC) define the specific criteria for the diagnosis of SSIs as purulent drainage, positive aseptic culture, or signs or symptoms of inflammation upon opening the incision beyond superficial cellulitis [2, 19].

The impact of infection on wound healing after breast reduction surgery ranges from minor complications, such as marginal necrosis, which is common at the junction of the inverted “T” incision, to major infections that require surgical intervention [23]. Many surgeons prefer to administer antibiotics, believing that it will reduce the incidence of these problems; however, previous studies suggest that antibiotic prophylaxis fails to reduce the rates of infection in clean surgeries, such as breast reduction [7, 14, 23–26].

Among studies conducted in different countries (United Kingdom, Ireland, Israel, and the United States), there was a tendency to prescribe prophylactic antibiotics beyond the intra- and postoperative periods (24 hours) of breast reduction, ranging up to 14 days. Cephalosporins were the most frequently prescribed, with the exception of the UK, which mentioned the use of amoxicillin/clavulanic acid in 70% of cases [9, 19, 21–23, 27–31].

Veiga-Filho et al. [32] compared SSI rates in patients receiving cephalexin for 7 days after hospital discharge (24 hours after breast reduction surgery) to patients who did not receive antibiotics. They observed significantly higher SSI incidence rates in the control group compared with the experimental group receiving antibiotics (14% vs. 2%, respectively; *p* = 0.03). They also observed that the incidence of SSIs was greater in older patients and in patients with a greater resected breast tissue mass (*p* = 0.02; *p* = 0.04, respectively) [32].

Reduction mammaplasty is an effective procedure that improves the quality of life for women with breast hypertrophy and is one of the most common plastic surgery procedures [33–36]. Prevention of SSIs is extremely important, because infection may compromise the outcome of the procedure, and increase the length of stay and costs of hospitalization [37].

This study was designed to address the lack of consensus on the role of antibiotics in breast reduction surgery. Despite the absence of solid evidence, the use of antibiotics following reduction mammaplasty is widespread, and a previous nonrandomized trial demonstrated higher SSI rates when no antibiotics were used. Thus, this trial was designed to compare the effectiveness of antibiotics prophylaxis for 24 hours with the extended use of antibiotics for 7 additional days.

The objective of this study is to evaluate the effect of postoperative antibiotic treatment on SSI prevention in breast reduction with perioperative prophylaxis.

## Methods/Design

This is a randomized clinical trial with two parallel, double-blind groups.

### Study setting

This single-center study is being conducted in the Academical Hospital of the Universidade do Vale do Sapucaí. The hospital is located in the urban area of Pouso Alegre, Minas Gerais, Brazil.

### Eligibility criteria

Patients who meet the eligibility criteria and provide their consent by signing an informed consent form are eligible to join the study.

#### Inclusion criteria

Female patients are included in this study if they are between 18 and 60 years of age, have a body mass index (BMI) between 19 and 30 kg/m^2^ and have breast hypertrophy according to the criteria of Sacchini ﻿et al. [38] and Franco and Rebello [39].

#### Exclusion criteria

Patients are excluded if they had previously undergone another surgical procedure of the breast, have been diagnosed with a breast pathology, are former smokers, have had a child or breastfed within the last year, have uncontrolled comorbidities, such as arterial hypertension or diabetes, or take immunosuppressants. Further, patients who misuse capsules or miss follow-up assessments will be excluded from analysis.

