### Adherence

#### Adherence reminder sessions

Face-to-face reminder sessions as to the importance of treatment adherence occur the day before surgery and at each weekly postoperative appointment. Such sessions include:Clear instructions are provided for all prescriptions and, after asking whether the patient has any questions, the patient is asked to repeat the instructions in their own words.The confirmation about the correct use of the capsules during the first 7 days of the postoperative period.The importance of following medical recommendations on the use of the bra and surgical wound care.The questioning of possible events that could constitute exclusion criteria as described in methods.

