### Allocation – concealment mechanism

A researcher, who will not participate in the care of patients, numbered the packages from 1 to 124 as per the randomly generated sequence. At the time of hospital discharge, each patient will receive a serial number and the corresponding numbered package containing the capsules that she will take.

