### Statistical methods – analysis population and missing data

Data analysis will be performed based on the original allocation of all patients as defined by randomization, regardless of the degree of adherence to the protocol (intention-to-treat principle). With respect to missing data, the amount thereof, their patterns and the variables associated with omission will define the most appropriate technique to be used in the processing of such data, whether in the primary analysis or the sensitivity analysis. For primary analyses, methods will be used that make use of all available data, such as multiple imputations.

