### Monitoring

In addition to the weekly evaluation regarding SSI, all the patients will be instructed to contact the assistant surgeon if they have any issue related to the operation or to the use of the capsules. In case of a diagnoses of SSI or if any problem related to the use of the capsules is recorded, the intake of the capsules will be immediately discontinued and the appropriate conduct will be taken in each case.

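### The protocol excludes patients who misuse capsules or miss visits from analysis, yet also commits to intention-to-treat using all available data; both rules cannot be followed.

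*Protocol article*

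**What the plan says.** The protocol article gives two rules for who is analysed.

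- **Exclusion criteria:** "Further, patients who misuse capsules or miss follow-up assessments will be excluded from analysis." The sentence closes the list of eligibility exclusions. It is not limited to a secondary or per-protocol analysis.
- **Statistical methods – analysis population and missing data** sets the other rule: "Data analysis will be performed based on the original allocation of all patients as defined by randomization, regardless of the degree of adherence." On missing data the same section adds: "For primary analyses, methods will be used that make use of all available data, such as multiple imputations."

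Three other sections bear on how the first rule would work.

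- **Allocation – concealment mechanism** fixes when treatment is assigned: "At the time of hospital discharge, each patient will receive a serial number and the corresponding numbered package containing the capsules that she will take."
- **Adherence reminder sessions**, held the day before surgery and at each weekly postoperative appointment, include this item: "The questioning of possible events that could constitute exclusion criteria as described in methods."
- **Monitoring** says that if an SSI is diagnosed or a capsule-related problem is recorded, "the intake of the capsules will be immediately discontinued". **Blinding** likewise suspends the capsules if an SSI is diagnosed during the course.

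The article does not define misuse. It does not say how many missed assessments lead to exclusion.

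**The concern.** The two rules conflict twice. On adherence, one drops the patient and the other keeps her. On missed visits, one drops her and the other uses whatever data she has. An analyst cannot follow both, and the article gives no order of precedence.

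The choice matters because both exclusion triggers arise after assignment. Randomisation makes the two groups comparable as assigned. A subset chosen by later behaviour no longer has that protection, even when everyone is blinded, because adherence and attendance may depend on how the patient is doing. Here there is one further route to bias. An infection or a capsule problem stops the capsules, so an incomplete course can be a consequence of the endpoint. If such a stop were counted as misuse, the rule would delete the events that the trial is meant to count.

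**Working it through.** **1. The two rules applied to the same patients**

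- *Takes the capsules wrongly, attends every visit, no SSI.* Exclusion criteria: out. Analysis population section: in, as a non-event.
- *Takes every capsule, misses one weekly visit.* Exclusion criteria: out, if one miss suffices. Analysis population section: in, on the data available.
- *SSI diagnosed during the 7-day course, capsules suspended as Blinding and Monitoring direct.* Exclusion criteria: unclear, because misuse is undefined. Analysis population section: in, as an event.

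The first case is a direct contradiction, and so is the second if one miss suffices. The third is an ambiguity that touches the endpoint itself.

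**2. Timing**

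The package is assigned at discharge. The capsules are taken over the next 7 days, and SSI is assessed weekly for the first 30 days. Both exclusion triggers therefore fall after assignment. The adherence sessions look for possible exclusion events at those postoperative visits, so the exclusion sentence is not merely a screening rule.

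**3. The plan's own figure**

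Sample size states 62 per group, 5% significance and 80% power, from the earlier study's 14% versus 2% (Background). With the pooled-variance formula, one-sided and without continuity correction:

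n = [1.645·√(2·0.08·0.92) + 0.842·√(0.14·0.86 + 0.02·0.98)]² / 0.12² ≈ 62.15

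This is 63 when rounded up, so the stated 62 is essentially reproduced. The sidedness is my inference, as the article does not state it. The figure contains no visible allowance for patients dropped from analysis. On this one-sided calculation, power is 79.9% at 62 per group. It would be 76.2% if 10% were removed from each group (56 analysed) and 71.9% if 20% were removed (50 analysed). Those shares are assumptions.

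**4. How many might be excluded**

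The article gives no miss rate. Assume four weekly visits within 30 days, exclusion after any single miss, independent misses, and a miss probability q per visit. The share excluded is 1 − (1 − q)⁴:

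- q = 2%: 1 − 0.98⁴ = 7.8%
- q = 5%: 1 − 0.95⁴ = 18.5%, or about 23 of 124
- q = 10%: 1 − 0.90⁴ = 34.4%

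**5. What exclusion could do to the result**

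At the planning rates, about 9/62 versus 1/62 SSIs gives a two-sided Fisher p = 0.017. Removing one, two or three placebo SSI patients, and nobody else, gives p = 0.017, 0.031 and 0.057. Three is the smallest number that crosses 0.05, so this is a deliberate worst case.

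It is also far from the trial's own data. Trial status reports 0 SSIs in 90 operated patients, leaving 124 − 90 = 34, or about 17 per group if allocation is even.

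- Expected placebo SSIs still to come at 14%: 17 × 0.14 = 2.4.
- Chance of 9 or more among 17 at 14%: about 0.0002.
- With no SSI in the antibiotic group, two-sided significance at 62 per group needs 6 placebo events (6/62 versus 0/62, p = 0.028; 5/62 versus 0/62, p = 0.057). The chance of 6 or more among 17 at 14% is about 2%.
- At 2/62 versus 0/62, p = 0.50.

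The significance verdict is therefore unlikely to depend on the population. The rates still can. With 2/62 (3.2%) observed, excluding one of those two patients gives 1/61 (1.6%), about half.

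**The case against.** The best defence is that intention-to-treat is named in the section devoted to the analysis population, while the exclusion is one sentence attached to an eligibility list, so a reader would let the former govern. That is the more natural order of precedence, but the article does not state it. The exclusion sentence refers expressly to analysis and carries no limitation.

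A second defence is that a patient who stops capsules because the protocol directs it has not misused them. That is a fair reading, and it limits what can be claimed. A reader might infer that the exclusions are tied to outcome and to treatment group. The documents do not establish this: misuse is undefined, and no section says that misuse or missed visits differ by group. Only the possibility stands.

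Third, 0 SSIs in 90 patients makes the practical effect look small. For the significance verdict, that is right. A reader might take the shift from p = 0.017 to p = 0.057 as what is at stake, but it rests on a one-sided removal and on an event count that the trial is very unlikely to reach.

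Fourth, the article reports adherence sessions and routine follow-up at the same clinics, so few visits may be missed. That may be so. The miss rates above are assumptions, and the article does not say that one miss is enough to exclude.

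Two further inferences should be resisted. The article reports no patient as already excluded under this rule. Nor is multiple imputation fixed as the method: it appears only as an example ("methods will be used that make use of all available data, such as multiple imputations"), with the technique to depend on the amount and pattern of missing data.

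**Conclusion.** The contradiction is certain and rests on the text alone: the article states two incompatible rules for who enters the comparison of SSI rates. It is equally clear that both exclusion triggers follow assignment, so applying the exclusion would give up the randomised comparison.

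That the exclusion would also remove endpoint events is conditional on a stop for SSI or for a capsule problem being counted as misuse. The article neither says so nor rules it out.

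The size is unknown. The 18.5% figure illustrates one set of assumptions and is not an estimate. Given the reported data, a changed significance verdict is improbable. What remains exposed is the pair of reported SSI rates, where one excluded event among very few would be plain to see, and the freedom to defend either population once allocation is revealed. The point should be settled before then, because it decides who is counted in the trial's main comparison.

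**What to change.** - Delete the Exclusion criteria sentence as an analysis rule.
- State that the primary population is all randomised patients, analysed by assigned package, and that every observed SSI counts regardless of capsule use or missed visits. This keeps the population already described in the analysis section.
- If an analysis of adherent patients is wanted, label it as a per-protocol sensitivity analysis. For that analysis, define misuse so that a stop directed by the protocol does not count, and say how many missed assessments remove a patient.
- Optionally, add a best-case and worst-case table for patients with missing 30-day SSI status, as a sensitivity analysis. The present wording on multiple imputation can stay.

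The cost is a short protocol amendment, made before allocation is revealed, and a few lines of analysis. The sample size stays at 124, and no treatment or follow-up procedure changes.

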## Interventions

### Surgical procedures

The patients will undergo reduction mammaplasty in the surgical center of the hospital of the Universidade do Vale do Sapucaí, by the same surgical team, lead by a single surgeon. The superomedial pedicle technique will be used to raise the nipple-areola complex [40].

All patients will be hospitalized the day before surgery and will take a shower with a 4% chlorhexidine antiseptic solution on the day of surgery [41, 42]. The operation will be performed under general anesthesia, and antisepsis of the operative field will be carried out with a 0.5% chlorhexidine alcohol solution [41, 42]. All patients will receive antibiotics intravenously during surgery and during their hospital stay (cephalothin, 1 g at induction of anesthesia and every 6 hours).

### Outcome procedures

On the first postoperative day, prior to hospital discharge, the assistant surgeon will remove the dressing from the incision and will instruct the patient on how to wash the wound daily with soap and water. Patients will also be instructed to wear a postoperative bra (MaCom® - Malhas de Compressão, Brazil - Ref 1002) for 30 days, and to avoid driving and working out for the same period.

After 24 hours, at hospital discharge, the assistant surgeon will give the patient a package with her protocol number, containing 28 capsules (cephalexin 500 g or placebo 500 g), and instruct her to take one every 6 hours for 7 days. Specially produced capsules containing either the antibiotic or placebo were kindly provided by Cimed Indústria de Medicamentos Ltda, São Paulo, Brrazil, who was not involved with design or conduct of this study in any other way.

### Adherence

#### Adherence reminder sessions

Face-to-face reminder sessions as to the importance of treatment adherence occur the day before surgery and at each weekly postoperative appointment. Such sessions include:Clear instructions are provided for all prescriptions and, after asking whether the patient has any questions, the patient is asked to repeat the instructions in their own words.The confirmation about the correct use of the capsules during the first 7 days of the postoperative period.The importance of following medical recommendations on the use of the bra and surgical wound care.The questioning of possible events that could constitute exclusion criteria as described in methods.

### Outcome measures

The CDC considers an infection to be an SSI when it appears to be related to the surgical procedure and presents within 30 days of the operation. If implants are inserted during the surgery, the time frame is extended up to a year after the surgery [1]. CDC classifies SSI into three categories, superficial incisional, deep incisional or organ/space SSI. In the present study, as none of the patients received an implant, requiring a delayed assessment, patients will be monitored for the occurrence of infection once a week for the first 30 days following surgery as assessed by a single surgeon, who is a senior plastic surgeon, with extensive experience in breast surgery. This surgeon will diagnose the presence or absence of SSI, thus dichotomizing the outcome as development of SSI (Yes/No). In case of a SSI, it will be classified according to CDC’s criteria, by the same surgeon [1].

### Sample size

The experimental and control groups were designed for 62 patients each to ensure a significance level of 5% and power of 80%. This was calculated based on the proportions observed in a previous study with and without the use of antibiotics after breast reduction [32].

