## Discussion

Breast reduction was the eleventh most performed cosmetic procedure in the United States in 2014 (American Society of Plastic Surgeons). It is classified as a “clean operation”, although it has higher rates of infection than other procedures in the same category [18].

Studies comparing factors that affect the occurrence of SSIs in breast surgeries such as smoking, use of a surgical drain, preoperative chemotherapy, breast reconstruction, and associated administration of antibiotic prophylaxis, have presented conflicting conclusions [17, 29, 37, 43–47]. In three SSI cohort studies the recruited patients had differences in risk factors, preventing a quality meta-analysis [17, 43, 48, 49]. Finally, most of the available studies are related to the treatment of breast cancer and not specifically to breast reduction, emphasizing the importance of this study.

We chose to exclude women who have risk factors for SSIs in an attempt to homogenize the sample, allowing us to isolate the postoperative prophylaxis factor. In addition, pre- and intraoperative care related to infection control will be taken, including antiseptic treatment of the operative field, routine antibiotic prophylaxis, hemostasis, care and caution to detachments, handling and preparation of the flaps without tension sutures and sterile dressing will be taken.

Short et al. [18] performed a meta-analysis on SSIs from reduction mammaplasties, and found only three randomized clinical trials. They concluded that preoperative antibiotic prophylaxis is effective in preventing SSIs in reduction mammaplasties; they determined a decrease in the incidence of SSIs of 75%, compared with placebo or no medication, and therefore recommended its use in clinical practice. Their meta-analysis also highlighted the importance of randomized controlled trials to evaluate the postoperative prophylaxis, which has yet to be done [18, 23, 29, 50].

As well as in other studies in which cephalosporins are the main used antibiotics following reduction mammaplasties, we chose to use two different first-generation cephalosporins: cephalothin, for intravenous use in the intraoperative period and the first 24 hours (1 g each 6 hours) and cephalexin for oral use (500 g every 6 hours) in the subsequent postoperative 7 days, compared to placebo [9, 19, 21–23, 27–31].

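### The sample size uses a 14% control rate from patients described as receiving no antibiotics; the protocol does not show that this rate applies to a placebo arm given 24 hours of IV cephalothin, so the unqualified 80% power is not supported

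*Protocol article*

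**What the plan says.** The Sample size section fixes the design in two sentences: "The experimental and control groups were designed for 62 patients each", chosen "to ensure a significance level of 5% and power of 80"%, with the rates taken from one earlier study: "This was calculated based on the proportions observed in a previous study with and without the use of antibiotics after breast reduction [32"].

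The Background supplies the rates, with the higher SSI incidence "in the control group compared with the experimental group receiving antibiotics (14% vs. 2%, respectively"). It describes that study's controls twice. The study compared 7 days of post-discharge cephalexin "to patients who did not receive antibiotics. They observed significantly higher SSI incidence rates in the control group". Later in the same section, "a previous nonrandomized trial demonstrated higher SSI rates when no antibiotics were used".

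The present trial gives perioperative cover to everyone. Under Surgical procedures: "All patients will receive antibiotics intravenously during surgery and during their hospital stay (cephalothin, 1 g at induction of anesthesia and every 6 hours"). The Abstract and the Discussion put this at 24 hours. The Background and the Discussion state the question as 24 hours of prophylaxis against the same plus 7 further days.

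The Discussion also cites a meta-analysis of preoperative prophylaxis in this operation: "they determined a decrease in the incidence of SSIs of 75%, compared with placebo or no medication".

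**The concern.** The sample size rests on a single pair of rates, and the control rate drives it. As the Background describes the source, 14% was seen in women given no antibiotics, whereas this trial's control arm has a day of IV cephalothin. The protocol accepts that preoperative prophylaxis lowers SSI substantially, so a rate without antibiotics cannot be carried into a covered arm without justification, and none is given.

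At stake is how a non-significant result will be read. The Discussion expects the results to support standard protocols for prophylaxis. If readers take the 80% at face value, they may treat a null result as evidence that the extra 7 days are unnecessary. If the control rate is well below 14%, the trial has little ability to show that either way.

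**Working it through.** **Inputs.** 62 per arm, 5% level (sidedness not stated) and 80% power, from Sample size. Rates of 14% and 2%, from Background. Chi-square or Fisher's exact test, from Statistical methods – outcomes. A 75% reduction with preoperative prophylaxis, from Discussion. No infections in 90 operated patients, from Trial status.

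**1. Reproducing 62 per arm.** Pooled-variance formula without continuity correction:

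n = [z_a·√(2p̄(1−p̄)) + z_b·√(p1(1−p1) + p2(1−p2))]² / (p1−p2)²

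with p1 = 0.14, p2 = 0.02, p̄ = 0.08 and z_b = 0.842.

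- One-sided 5% (z_a = 1.645): n = 62.1, or 63 when rounded up; approximate power at 62 is 79.9%.
- Two-sided 5% (z_a = 1.960): n = 79.0, or 80 when rounded up; approximate power at 62 is 69.7%.

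The stated size therefore matches 14% vs 2% only with a one-sided 5% test, which the article does not mention. The other two-sided variants tried gave 77 (unpooled), 68 (arcsine) and 95 (continuity-corrected).

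**2. Power of the planned test at the borrowed rates.** All 63 × 63 possible outcome tables for 62 per arm were enumerated with binomial weights, and the probability of those with two-sided p ≤ 0.05 was summed. At 14% vs 2%, power is 59.6% (Fisher) and 74.9% (uncorrected chi-square). Neither reaches 80%, whatever cover the source controls had.

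**3. What follows if the source controls had no cover.** The documents give no SSI rate for a control arm with 24 hours of cover, so the control rates below are assumptions: 14% reduced by a quarter, by a half, and by the cited 75% (0.14 × 0.25 = 0.035). The antibiotic rate is the control rate times 2/14, which keeps the planned relative effect.

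| Control vs antibiotic | Fisher | Chi-square |
|---|---|---|
| 14% vs 2% (borrowed) | 59.6% | 74.9% |
| 10.5% vs 1.5% | 39.5% | 59.3% |
| 7% vs 1% | 16.6% | 39.7% |
| 3.5% vs 0.5% | 1.6% | 12.7% |

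A count explains the last row. With no infections in the antibiotic arm, significance needs at least 6 control infections by Fisher or 4 by chi-square. At 3.5% the expected number is 62 × 0.035 = 2.2.

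**4. The trial's own data.** With 0 infections in 90 patients, the one-sided 95% upper limit for the pooled rate is 1 − 0.05^(1/90) = 3.3%. The design implies (14% + 2%)/2 = 8%. Under 14% and 2%, assuming a 45/45 split, the probability of no infection is 0.86^45 × 0.98^45 ≈ 0.0005. This does not fit the borrowed rates, but the data are pooled over arms and do not identify the cause.

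**The case against.** The strongest reply is that there may be no mismatch. The Background defines the earlier study's treated group by 7 days of cephalexin starting at discharge, 24 hours after surgery, which is this trial's own experimental course. Its controls may simply have gone without that course. The Sample size sentence speaks of antibiotic use after the operation, and the Background moves directly from the earlier study to this trial's 24-hour comparison, as if the question were the same. This reading is plausible and the source is not at hand, so it cannot be excluded. But no part of the article states it, and the Background's two descriptions, read plainly, say otherwise.

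Three stronger inferences are tempting and are not supported:

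- **That 14% vs 2% necessarily mixes a perioperative effect with the extended course.** This requires cover in the source's treated group and none in its controls, which the article nowhere says. If neither group had cover, the contrast still isolates the 7-day course and only the baseline risk differs.
- **That 3.5% is the protocol's rate for its placebo arm.** It multiplies one study's rate by another review's reduction. If the source controls did have cover, it discounts twice.
- **That a null result is nearly certain, or that power always falls by more than 20 points.** At 10.5% vs 1.5% the chi-square loss is 74.9 − 59.3 = 15.6 points. At 10.5% vs 0% power is 64.5 / 90.2%, above the figures at the borrowed rates.

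The shortfall at 14% vs 2% itself comes from the unstated one-sided calculation and should not be charged to the comparator.

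**Conclusion.** The point holds as a gap in justification; it does not establish that the trial was sized for a different comparison. The protocol takes its control rate from women it twice describes as having no antibiotics, gives its own controls 24 hours of IV cephalothin, and does not bridge the two. The unqualified 80% power is therefore not supported.

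Two parts of the size should be kept apart. The first does not depend on the source: exact two-sided power at 14% vs 2% is 60 / 75%. The second is conditional on uncovered source controls: at the planned 1/7 risk ratio, power runs from 39 / 59% down to 2 / 13% as the assumed control rate goes from 10.5% to 3.5%. The documents cannot fix where in that range the trial lies.

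**What to change.** Keep n = 124 and change the text only.

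1. Reconcile Background and Sample size by stating whether the earlier study's controls had perioperative antibiotics. If they did, correct the two Background descriptions.
2. Replace the 80% claim in Sample size with the power of the planned test at 62 per arm, two-sided 5%: 60% (Fisher) or 75% (uncorrected chi-square) at 14% vs 2%. If the source controls had no cover, add the range in the table above, labelled as assumed control rates, with 3.5% identified as 14% reduced by the 75% cited in the Discussion.
3. State in the Discussion that a non-significant result cannot be read as showing that 24 hours of prophylaxis is sufficient.

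The cost is a reworded sample-size paragraph, a clarifying clause in the Background and one sentence in the Discussion. No patients or procedures are added. The price is a less favourable stated power.
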